## 6 STUDY INTERVENTION

### 6.1 STUDY INTERVENTION(S) ADMINISTRATION

#### 6.1.1 STUDY INTERVENTION DESCRIPTION

Vosoritide, also known as BMN 111 or modified recombinant human C-type natriuretic peptide (CNP), is a 39-amino-acid peptide analog that includes the 37 C-terminal amino acids of the human CNP53 sequence plus the addition of 2 amino acids (Pro-Gly) on the N-terminus. This structural modification conveys resistance to neutral endopeptidase (NEP) degradation, resulting in prolonged half-life ( $t_{1/2}$ ) in comparison to endogenous CNP. This increase in  $t_{1/2}$  allows once daily subcutaneous (SC) administration.

Vosoritide is currently an investigational drug and is not commercially available.

#### 6.1.2 DOSING AND ADMINISTRATION

During the study, vosoritide will be administered as a single 15  $\mu\text{g}/\text{kg}$  subcutaneous injection given daily at approximately the same time each day whenever possible. The time of day of administration will be up to the individual subject and their guardian. It will be given 7 days per

week. The same injection site should not be used 2 days in a row, and sites should be rotated. Doses may be administered in any of the common subcutaneous areas (upper arm, thigh, abdomen, buttocks). If a dose is missed and noticed within 12 hours of the missed dose, it should be given at that time. If it has been more than 12 hours since the time of the missed dose, that dose should be skipped and the regular dose should be given the following day.

Vosoritide will be given for an initial 12-month period followed by an extension phase until cessation of growth or subject withdrawal from the study or until vosoritide becomes commercially available for the subject's indication. Doses will be given in the clinic during the Day 1, Day 2, 6 Month and 12 Month Visits prior to pharmacokinetic sampling. At the 6 month visit, the subject will be weighed. The dose of medication will be recalculated using the same 15 µg/kg dose but adjusted for the new weight. There will be no other dose increases in the protocol. After consultation with the DSMB, the dose may be reduced by 20% if the subject meets the individual stopping criteria on one occasion as detailed in **Section 7.1** below.

Subjects with a good response at 12 months will be offered participation in the extension phase of the study. A good response is defined in the inclusion criteria above. Subjects in the extension phase will continue to be seen in-person every 6 months at Children's National with telephone visits at the 3-month time point mid-way between in-person visits.

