Additional assessments noted in the prior paragraph will be repeated at the 6 and 12 month visits as detailed in the protocol. The dose of medication will be adjusted for weight at the 6 month visit if the subject has experienced weight changes.

During the extension phase, subjects will continue to be seen at Children's National every 6 months until growth cessation or subject withdrawal. Telephone visits will occur at the 3-month time point mid-way between each study visit.

**Study Duration:** 36 months; Extension phase of study may last up to an additional 15 years  
**Participant Duration:** 18 months; Extension phase may last up to ~15 years if a subject starts at age 3 years and stops growing at age 18 years

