| Dose Adjustment g                                   |                                                                            |                                 | X                                                                     |                                 | X                                                                     |                   |

Note: The schedule for the extension phase repeats every year with alternating telephone and in-person visits every 3 months. a All treatment visits have pre-dose vital sign assessments. Vital signs include: body temperature in degrees Celsius (°C), heart rate, BP, and respiratory rate. Vital sign measurements are taken in a sitting position after at least 5 minutes of rest. Vital signs should be measured before blood samples are drawn. Vital signs may be monitored more frequently or for longer duration post-dose as clinically indicated.

b Anthropometric measurements include standing height, weight, sitting height, head circumference and arm span. Standing height should be measured 5 times using a calibrated stadiometer. Sitting height should be measured three times. Weight should be measured on a digital scale.

c Clinical labs include: complete blood count with differential, complete metabolic panel, lipid panel, TSH, free T4, IGF-I, IGFBP-3, prolactin. All labs will be obtained through the clinical lab at Children's National Hospital. Additionally, an extra 10 cc of blood will be obtained for storage for future analysis.

d PD: Serum collagen X marker measurement will be obtained at all in-person visits.

e DXA scan will include whole body less head as well as a lumbar spine DXA. It will be done every 24 months.

f Additional safety imaging may include echocardiograms, spine X-rays or any musculoskeletal imaging that is needed based on a clinical concern of the investigator.

g Vosoritide dose will be adjusted for weight at every in-person visit to maintain the prescribed dose of 15 µg/kg/day

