After PI consultation with the DSMB, the subject may be re-challenged with a 20% dose reduction for any AE which may be dose related and is reversible with dose decrease (such as hypotension). If excessive increase in growth, worsening of scoliosis or other conditions related to bone overgrowth are noted, vosoritide will be discontinued permanently, and the subject will be followed-up off treatment for the duration of the study. If the subject meets stopping criteria on re-challenge or if the subject refuses re-challenge, the subject will be permanently discontinued from the medication with ongoing assessment in the study.

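### Both weight-recalculation rules name a fixed 15 µg/kg, and nothing says which level applies to a child whose dose was reduced by 20%

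*Protocol*

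**What the plan says.** **Weight recalculation, main phase.** Section 6.1.2, for the 6 month visit: "The dose of medication will be recalculated using the same" 15 µg/kg, adjusted to the new weight. The Synopsis (Section 1.1) describes the same step conditionally: "The dose of medication will be adjusted for weight at the 6 month visit if the subject has experienced weight changes". Section 6.1.2 then adds: "There will be no other dose increases in the protocol".

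**Weight recalculation, extension.** Footnote g to the extension Schedule of Activities (Section 1.3): "Vosoritide dose will be adjusted for weight at every in-person visit to maintain the prescribed dose of" 15 µg/kg/day.

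**Dose reduction.** Section 6.1.2: after DSMB consultation, "the dose may be reduced by 20% if the subject meets the individual stopping criteria on one occasion". Section 7.1, Individual Subject Stopping Criteria, limits this to a class of events: "the subject may be re-challenged with a 20% dose reduction for any AE which may be dose related and is reversible with dose decrease". It then sets the consequence of a further event: "If the subject meets stopping criteria on re-challenge or if the subject refuses re-challenge, the subject will be permanently discontinued" from the medication, with assessments continuing.

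**Cohort-wide reduction.** Under Study Suspension Criteria, Section 7.1 lists a dose decrease for everyone among the recommendations open to the DSMB.

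The Protocol does not say how long an individual reduction lasts, which µg/kg level is used when a reduced child is re-weighed, or whether and how a reduced child may return to 15 µg/kg.

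**The concern.** A child on a reduced dose falls under two instructions that do not fit together. One lowers the dose by 20% after an event that may be dose related. The other recalculates at 15 µg/kg without exception. Section 6.1.2 contains both and does not say which prevails.

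Three things are at stake:

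- **Oversight.** The decrease requires DSMB consultation. No consultation is written for a return to the starting level.
- **The permanent-discontinuation rule.** It applies to a child who again meets stopping criteria on re-challenge. If re-challenge means treatment at the reduced dose, the status of a child recalculated to 15 µg/kg is undefined.
- **Safety data.** Safety and tolerability, with attention to hypotension, is a primary objective. If reduced children are handled differently from one case to the next, the dose at the time of an event becomes harder to interpret.

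**Working it through.** No sample size, power or alpha figure is involved, and the Protocol states no figure of its own to reproduce. The check is simple arithmetic plus a comparison of the texts.

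**1. Inputs from the Protocol.** Dose level 15 µg/kg/day (Sections 6.1.2 and 1.3). Reduction 20% (Sections 6.1.2 and 7.1). Recalculation at Month 6 (Sections 1.1 and 6.1.2) and at each in-person extension visit, every 6 months (Section 1.3, footnote g).

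**2. Reduced level.** 15 × (1 − 0.20) = 12 µg/kg.

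**3. Literal recalculation.** 15 / 12 = 1.25, a rise of 25% per kg over the reduced level.

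**4. Absolute dose.** If weight goes from w0 to w1, the dose relative to the reduced dose is 1.25 × (w1/w0) when recalculated at 15 µg/kg, and w1/w0 when recalculated at the reduced level. The weights below are assumptions; the Protocol gives none.

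| Weight, kg | Starting dose, µg | After 20% cut, µg | Recalculated at 15 µg/kg | Recalculated at 12 µg/kg |
|---|---|---|---|---|
| 12 to 12 | 180 | 144 | 180 (+25%) | 144 (0%) |
| 12 to 13 | 180 | 144 | 195 (+35%) | 156 (+8%) |
| 15 to 16 | 225 | 180 | 240 (+33%) | 192 (+7%) |
| 20 to 21.5 | 300 | 240 | 322.5 (+34%) | 258 (+8%) |
| 25 to 27 | 375 | 300 | 405 (+35%) | 324 (+8%) |

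The first row arises only under the Section 6.1.2 wording. The Synopsis makes a weight change the condition for adjusting, so the two descriptions differ slightly there as well.

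**5. When, and how often.** In the main phase, recalculation is described only at Month 6. None is described at Month 12, and the Dose Adjustment row of the extension schedule has no mark at the initiation visit, which falls on the same day. So:

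- A child reduced before Month 6 meets the rule at Month 6.
- A child reduced between Month 6 and Month 12 meets it at the first in-person extension visit, 6 months after Month 12, and only if the child qualifies for and enters the extension.
- A step from 12 to 15 µg/kg can happen once. Later visits then only track weight. A second reduction is not foreseen, because meeting stopping criteria on re-challenge leads to permanent discontinuation.

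**6. Does the sentence on other increases settle it?** Take the two possible meanings of dose in "There will be no other dose increases in the protocol":

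- If it means the amount in µg, the Month 6 recalculation is the one permitted increase. The sentence then conflicts with footnote g, which raises the amount at every extension visit of a child who gains weight.
- If it means the µg/kg level, the sentence bars a move from 12 to 15. But then the word other has nothing to refer to, because for a child not reduced the Month 6 recalculation leaves the level unchanged.

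Neither meaning fits all the text, so the sentence cannot decide the matter.

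**7. Cohort-wide decrease.** The fixed 15 µg/kg in both rules also makes no allowance for a DSMB decrease for all subjects. The Protocol gives no size for such a decrease, so no figure is attached.

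**The case against.** A reader might infer that the Protocol orders every reduced child back to 15 µg/kg at the next visit, and again at each 6-monthly visit. The documents do not support that. No sentence orders re-escalation. The reduction sentence comes after the recalculation sentence in Section 6.1.2 and can be taken as the specific exception to a general rule. The Synopsis makes a weight change the trigger, and moving from 12 to 15 µg/kg is not a weight change. The timing is limited, and a reset would occur once (step 5). These points stand, and they limit the finding to a literal reading of text that is open to another.

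Four further points deserve weight:

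- **Few children may be affected.** Re-challenge is limited to events that may be dose related and reverse with a lower dose; overgrowth and worsening scoliosis lead to permanent discontinuation. The Protocol gives no expected number of reduced children.
- **The DSMB is not absent.** It receives adverse event reports and meets at least every 6 months (Sections 8.3.5 and 10.1.6). That is general oversight, though, and not a consultation on one child's return to a higher dose.
- **The data may be adequate.** A reader might infer that dose at event could not be recovered. The case report forms are described in a manual that is not shown (Section 10.1.9.1), and individual data are to be listed by time point (Section 9.4.8). At most, interpretation becomes harder.
- **The alternative reading is plausible.** It does not close the gap, because the sentence it relies on conflicts with footnote g. Both recalculation rules are written as mandatory, with a fixed number.

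**Conclusion.** The concern holds as an unresolved conflict in the dosing text. Both recalculation rules name 15 µg/kg and exempt neither a child reduced by 20% nor a cohort reduced on DSMB advice. Followed literally, they would undo an individual reduction once: 12 to 15 µg/kg, or +25% per kg. Under the assumed weight gains, the absolute dose would rise by about 33% to 35%, against about 7% to 8% if the reduced level were kept. The 25% follows from the Protocol's own figures; the larger range rests on the assumed weights. No DSMB consultation is specified for the increase, and the status of such a child under the permanent-discontinuation rule is unclear.

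The number of children affected is unknown and may be small. The point still warrants correction, because it concerns children who have already met a stopping criterion. It is also a dosing instruction that belongs in the Protocol, not something left to a statistical analysis plan. Which level is right is a clinical decision and is not judged here.

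**What to change.** Reconcile the Synopsis (Section 1.1), footnote g in Section 1.3, Section 6.1.2, and both the individual and the study-level rules in Section 7.1, so that they state:

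1. which assigned µg/kg level the weight recalculation uses after an individual reduction or a DSMB decrease for all subjects;
2. whether any later increase from a reduced level is allowed and, if so, whether it needs DSMB consultation;
3. whether a child whose level has changed since the reduction still counts as on re-challenge for permanent discontinuation;
4. how the statement excluding other dose increases relates to weight adjustment in the extension.

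Confirm that the assigned µg/kg level is recorded at each visit; the forms are not shown, so this may already be the case.

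The cost is a wording change at the next amendment, with no added visits or subjects.

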## 6.2 PREPARATION/HANDLING/STORAGE/ACCOUNTABILITY

### 6.2.1 ACQUISITION AND ACCOUNTABILITY

Vosoritide will be supplied by BioMarin to the Investigational Pharmacy at Children's National Hospital in sterile, single-dose, Type I glass vials with coated stopper and flip-off aluminum cap. Vosoritide drug product is supplied as a lyophilized, preservative-free, white-to-yellow powder for reconstitution with pre-filled sterile water for injection syringes. BioMarin will provide all additional necessary supplies for drug administration. The study team will work closely with the investigational pharmacy to monitor drug supply. Details of needed supplies and protocol for requesting additional drug from BioMarin will be detailed in a Pharmacy Manual prior to initiation of the study.

The investigational pharmacy will distribute 3 month supplies of medication, pre-filled sterile water for injection syringes, syringes and all necessary supplies to each study subject via the investigator at the baseline and 6 month study visits and at all in-person extension study visits. An additional 3 month supply will be shipped to the subjects at months 3 and 9 of the study and at the necessary intervals during the extension phase. Drug and supplies will be packed and shipped overnight from the IDS with the assistance of the study team via FedEx. Study drug kits and supplies do not require refrigeration during transportation from the IDS to the subject's home, but must be refrigerated when stored at the subject's home. Additional details regarding all these aspects will be provided in the Pharmacy Manual. The study team will contact the family the day after shipping to ensure that undamaged product and supplies were received. At the 6 month and 12 month visit and all in-person extension study visits, the subjects will return any used (empty) and unused drug product vials, unused sterile water for injection syringes, and unused supplies to the investigator which will then be counted as a measure of drug administration compliance. At the 12 month study visit or at the final study visit in the extension study, used (empty) and unused study drug, unused pre-filled sterile water for injection syringes, and supplies will be returned to the investigational pharmacy for disposal. At the conclusion of the entire study,

unused drug will either be returned to BioMarin or destroyed as per standard operating procedure of the investigational pharmacy.

---

#### 6.2.2 FORMULATION, APPEARANCE, PACKAGING, AND LABELING

Vosoritide is cloned into the pJexpress401 vector, expressed in *E. coli* and then purified. The drug substance is a modified CNP peptide that retains wild-type activity and specificity. The modified CNP sequence is:

PGQEHPNARKYKGANKKGLSKGCFGLKLDRI GSM SGLGC

The amino acid sequence is an analogue of the naturally occurring tissue-expressed form of C-type natriuretic peptide (CNP-53). Vosoritide is a recombinant 39 amino acid peptide that includes the 37 C-terminal amino acids of the human CNP-53 sequence, and is engineered to include two additional amino acids (Pro-Gly) on the N-terminus, which renders the peptide more resistant to degradation. It is a cyclic peptide formed by an intramolecular disulfide bond. The molecular weight of the purified product is 4.1 kDa.

The clinical drug product will be supplied in sterile, single-dose, Type I glass vials with coated stopper and flip-off aluminum cap. The vial will have a label stating "Caution: New Drug--Limited by Federal (or United States) law to investigational use." Vosoritide drug product is supplied as a lyophilized, preservative-free, white-to-yellow powder for reconstitution with pre-filled sterile water for injection (WFI) syringes. The reconstituted solution is colorless to yellow and contains 0.8 mg/mL to 2 mg/mL of vosoritide, as well as citric acid, sodium citrate, trehalose, mannitol, methionine, polysorbate 80, and sterile WFI. The target pH of the reconstituted solution is 5.5. Sterile WFI will be supplied in a pre-filled diluent syringe. All reconstitution and dose preparation steps will be performed as indicated in the vosoritide Injection Guide and Injection video. The subjects and their guardians will be trained in proper techniques for drug reconstitution and administration during the Day 1 Visit. Practice supplies will be provided along with educational materials. The subjects or their guardian will be required to demonstrate proper technique during the educational session. At the 6 month visit, we will review administration technique.

---

#### 6.2.3 PRODUCT STORAGE AND STABILITY

Lyophilized vosoritide should be stored in a restricted area at refrigerated temperature (2°C-8°C; 36°F-46°F). All reconstituted vosoritide must be administered as a SC injection within 3 hours of reconstitution. Drug will be provided in a secure lock box which also contains a temperature monitor. Details of drug storage and temperature monitoring will be provided in the Pharmacy Manual. A drug administration log will be provided to the participants on which they will record the temperature information as well as the timing of reconstitution, timing of drug administration and administration site.

---

#### 6.2.4 PREPARATION

Details of study drug preparation are available in the separate pharmacy guide. All reconstitution and dose preparation steps will be performed as indicated in the vosoritide Injection Guide and accompanying video which will be provided to study participants. Complete details of all study drug handling will be in the study SOP. In brief, vosoritide must remain at 2-4 degrees Celsius at all times. The study drug will be shipped by BioMarin to the investigational pharmacy where it will be kept in cold storage with appropriate monitoring of temperature. A 3 month supply will be dispensed to the family at Visit Day 2 in a special cooler which will maintain the appropriate temperature during transport to the family's home. Each day, the family will remove a single vial from the study drug box. After allowing the

vial to sit at room temperature for 30 minutes, the parent/guardian will add the contents of the diluent syringe into the vial with vosoritide and then swirl the vial until all drug is dissolved. They will then let the vial sit for 5 minutes before drawing the correct dose of medication into an injection syringe.

### 6.3 MEASURES TO MINIMIZE BIAS: RANDOMIZATION AND BLINDING

Not applicable. This is an open label proof of concept study. There is no planned randomization or blinding.

### 6.4 STUDY INTERVENTION COMPLIANCE

Adherence to the protocol will be monitored in a number of ways. First, subjects will be given a drug log in which they will record each day's administration including timing of drug reconstitution, time of administration, temperature confirmation, and site of administration. Second, we will have periodic telephone calls with the subjects during which medication adherence will be reviewed (See Schedule of Activities, **Section 1.3**). Third, subjects will be asked to bring all remaining medication vials to the 6 and 12 month study visits and all extension phase in-person visits. Vial counts will be performed as a measure of compliance.

### 6.5 CONCOMITANT THERAPY

For this protocol, a prescription medication is defined as a medication that can be prescribed only by a properly authorized/licensed clinician. Medications to be reported in the Case Report Form (CRF) are concomitant prescription medications, over-the-counter medications and supplements. Concomitant therapy will be monitored at all study visits as outlined in the Schedule of Activities, **Section 1.3**. Concomitant medications prohibited during this study include growth hormone, aromatase inhibitors, gonadotropin releasing hormone analogs, recombinant IGF-1, oxandrolone, testosterone, and all forms of estrogen treatment.

#### 6.5.1 RESCUE MEDICINE

Not applicable

## 7 STUDY INTERVENTION DISCONTINUATION AND PARTICIPANT DISCONTINUATION/WITHDRAWAL

### 7.1 DISCONTINUATION OF STUDY INTERVENTION

Discontinuation from vosoritide does not mean discontinuation from the study, and remaining study procedures should be completed as indicated by the study protocol. If a clinically significant finding is identified (including, but not limited to changes from baseline) after enrollment, the investigator or qualified designee will determine if any change in participant management is needed. Any new clinically relevant finding will be reported as an adverse event (AE).

The data to be collected at the time of study intervention discontinuation are outlined in the Early Termination visit in the Schedule of Activities, **Section 1.3**.

